### Sample size

Sample size calculation was based on the primary endpoint: the proportion of patients who receive chemotherapy during their last 3 months of life (Table 1). This took into consideration the predetermined number of 12 as the total number of clusters, i.e. hospitals, that was chosen for contingency/feasibility reasons and allowing for intra-cluster correlation coefficient (ICC) in the range of 0.06–0.09, which is usually considered appropriate for process outcomes. In addition, calculations were performed to provide 80% power at the two-sided 5% level to detect a 25% difference in chemotherapy use between the two arms, i.e. 20% versus 45% in the treatment and control groups, respectively [61]. The choice of the clinically relevant treatment effect used for sample size calculation (25% difference for chemotherapy administration) was based on both clinical judgment and previous data [62, 63]. Effects on power increase due to adjustment by baseline measurements and other covariates (see statistical analysis section for the full list of covariates proposed) were also considered, allowing for correlation coefficient between outcome and adjustment covariates (r_adj_) up to 0.4. Table 2 reports sample size per treatment arm for various values of ICC and (r_adj_).

**Table 2 Tab2:** Sample size per treatment arm for various values of ICC and (r_adj_)

			**r**_**adj**_		
	*0.4*	*0.3*	*0.2*	*0.1*	*NO*^a^
**ICC**					
*0.06*	102	120	138	150	150
*0.07*	126	150	180	198	204
*0.08*	156	204	258	**300**^b^	312
*0.09*	210	318	468	630	714

*ICC* intra-cluster correlation coefficient, *r*_*adj*_ correlation coefficient between outcome and adjustment covariates

^a^No adjustment for baseline covariates

^b^Required no. of patients per arm

A sample size of 300 patients in each arm, with a total of 600 patients, was chosen as it accounts for an ICC up to 0.08 even with a low r_adj_ (no less than 0.1) and for an ICC up to almost 0.09 in case of r_adj_ no less than 0.3. Due to an expected attrition rate up to 12%, 340 patients per arm (680 in total) will be enrolled.

The 12 hospitals were grouped into three strata according to size of catchment area, to decrease the chance of imbalance in cluster characteristics between trial arms. Each cluster consisted of four hospitals: small (69,000–136,000 inhabitants); medium (169,000–282,000 inhabitants); and large (300,000–492,000 inhabitants) (Table 3). This procedure is considered a reliable and easy to measure proxy for other cluster characteristics, potentially impacting on the study outcome. Effect of the variability in cluster size (mean 50, SD 19.5, CV [Coefficient of variation] = 0.39) was calculated through the approach proposed by Van Breuckelen [64]. For CV = 0.39, this method indicates low inflation factors which are in the range of 2.8%–2.2%, for ICC in the range of 0.06–0.09, respectively [64]. The role of the correlation coefficient in sample size formula for binary outcomes and when adjusting for baseline factors is explained by Hemming et al [65]. Sample size calculations in Table 2 were undertaken using the module clustersampsi [65] implemented in the statistical package Stata (Stata Statistical Software, Release 14, Stata Corp., College Station, TX, USA).

**Table 3 Tab3:** Presentation of stratification, randomization results, and sample size at cluster level

Intervention arm				Control arm			
Hospital	Stratification	Inhabitants	Patients	Name	Stratification	Inhabitants	Patients
Stavanger University Hospital, Stavanger	1	352,650	85	Akershus University Hospital, Nordbyhagen	1	490,000	85
Oslo University Hospital	1	340,000	85	St. Olavs Hospital/Trondheim University Hospital, Trondheim	1	300,000	85
Østfold Hospital Trust, Grålum	2	282,600	50	Sørlandet Hospital, Kristiansand	2	170,000	50
Vestfold Hospital Trust, Tønsberg	2	233,000	50	Telemark Hospital Trust, Skien	2	169,000	50
Nordland Hospital Trust, Bodø	3	136,000	35	Førde Hospital Trust, Førde	3	109,000	35
Ålesund Hospital Trust, Ålesund	3	104,000	35	University Hospital of North Norway, Tromsø	3	125,000	35
**Total patients**			**340**	**Total patients**			**340**

### Eligibility criteria

The randomization process in C–RCTs consists of two levels: first, the clusters where the randomization takes place, *here: the hospitals*; then, the individual participants, *here: cancer patients*.

### Inclusion criteria: cluster level

Three explicit eligibility criteria apply to hospitals on the cluster level:
The hospital should have established both oncology and PC programs:
aAccording to Norwegian healthcare policy, the latter implies that the program consists of an ambulatory specialist PC team consisting of at least one physician and one nurse. The team serves the hospitals’ inpatients and may also engage in extra-mural activities;The hospital should have PC programs including EoL care;The hospital should have a local catchment area (as opposed to being a referral center only), meaning that a defined proportion of their cancer patients receive all cancer treatment in this hospital and are not transferred shortly after diagnosis for further treatment and follow-up elsewhere.

Further, it was an explicitly stated criterion for funding in the call that all four Norwegian health regions should be represented. Thus, this is considered on the cluster level of the trial.

### Study population

#### Inclusion criteria: participant level

##### Patients

At the second level of the C-RCT, the following eligibility criteria apply to patient inclusion:
A verified metastatic or locally advanced cancer of the upper gastrointestinal (GI) tract, lower GI tract, pancreas, liver, breast, bladder, prostate, kidney, cholangiocarcinoma, or malignant melanoma;Defined as a patient in need of PC with an anticipated life expectancy of < 12 months;Scheduled to start the anticipated last line of chemotherapy (definition: tumor directed systemic therapy). Time of inclusion that is based on the decisions about last line of chemotherapy, varies by diagnosis, and is equivalent to first line in some diagnoses;Age > 18 years;Fluency in written and oral Norwegian;Physically and cognitively able to provide written consent, based on clinical criteria, e.g. not too frail or having signs of disorientation, confusion, attention deficit, poor coordination;Scheduled to receive all oncological and specialized palliative treatment at the participating hospital, i.e. residing in the local area of the including hospital;WHO performance status 0–2.

Because gynecological and lung cancer patients receive anticancer treatment at the departments of lung and gynecology in most hospitals, these diagnoses were not included.

##### Caregivers

In this study, a caregiver is defined as “the person in a close supportive role sharing the illness experience with the patient, according to the patient.” Thus, this may not necessarily be a relative, although it most often is. Caregivers will be identified by asking the patient whom he or she identifies as the primary caregiver. Study personnel will then ask permission from patients who consent to the study if it is OK to ask his/her caregiver to participate as well. If a caregiver declines to participate, the patient can still be included and followed in the study.

The following set of eligibility criteria applies to the inclusion of caregivers:
Defined by the patient as the primary caregiver;Age > 18 years;Fluency in written and oral Norwegian;Physically and cognitively able to provide written consent, based on clinical criteria, e.g. not too frail or having signs of disorientation, confusion, attention deficit, poor coordination.

#### Exclusion criteria: participant level

Any serious psychiatric diagnosis (e.g. psychotic, bipolar disorder), substance abuse, or cognitive impairment as judged by standard clinical criteria (disturbed consciousness, disorientation to time/place and attention deficits) that precludes completion of PROs, at the discretion of the attending physician/study personnel;A cancer diagnosis other than the ones specified in the inclusion criteria (patients);Multiple malignancies (patients);Already included and followed in a PC program (all);Serious substance abuse (all).

#### Randomization, blinding, and study monitoring

Randomization was performed within each stratification group using a web-based randomization system developed and administered by the Unit for Applied Clinical Research, Institute of Cancer Research and Molecular Medicine, Norwegian University of Science and Technology (NTNU), Trondheim, Norway. The procedure was concealed for all study personnel. The allocation of hospitals to the intervention and control arms is shown in Table 3.

### The complex intervention

The complex intervention in the PALLiON study consists of three separate, but highly integrated, parts that will be performed in the six hospitals randomized to the intervention arm:
An educational program for involved oncologists and PC physicians and nurses;A patient care pathway, mapping treatment and care activities from inclusion through follow-up, thereby consolidating an integration of PC and oncology;Systematic symptom assessment in all consultations, preferably computer-based.

### The structured educational program

The aims of the educational program are to provide the participants—i.e. oncologists, doctors under specialization, PC physicians and residents—with sufficient competence, theoretical knowledge, understanding, and practical skills to make a complete integration of oncological care and PC in the PCCPs. The content of the program is specifically selected as they represent transitions in a disease and treatment trajectory, e.g. in relation to discontinuation of treatment and disease progression, and that are often perceived as difficult by clinicians, such as communication of prognosis and breaking bad news. Thus, the content of the lectures correspond with the organization of care and the specific content at each step of the PCCSs. Hence, the program is to be completed before patient inclusion in the PALLiON study, with a mandatory confirmation that it has been completed.

The educational program takes place at each of the six intervention hospitals. It consists of classroom lectures, Internet teaching videos, group work, and 1 day with communication skills training focusing on specific communication tasks related to integration of oncology and PC. The first of the eight lectures is a thorough introduction lecture presenting the scientific basis, organization, methods, and objectives of the PALLiON study. The following seven focus on central issues related to palliative treatment. They have an overall duration of 3 h, use the PowerPoint format, and are taped with voice-over to make them available in the e-learning program (see below). All lectures are given by experienced physicians who are specialists in oncology and/or PC and with long-standing clinical experience. The content is based on evidence-based treatment guidelines on chemotherapy and radiotherapy endorsed by the ASCO [66] and the American Society for Radiation Oncology [67], symptom assessment, and relevant literature related to each subject. The following areas are covered: (1) PALLiON—care pathways and integration of PC and oncology; (2) the educational program—objectives, structure, content, short info about Eir; (3) using Eir in clinical practice, symptom assessment; (4) prognostication, prognostic tools; (5) palliative radiotherapy; (6) palliative chemotherapy; and (7) EoL care.

The e-learning program follows the structure of the one at the Faculty of Medicine at the University of Oslo and has an overall duration of 3 h. Four videos are used, in which a young patient with breast cancer is followed. An experienced nurse plays the patient while an experienced oncologist and an experienced PC physician feature the consulting physicians. The first video starts when the patient comes to the oncologist after having completed third-line chemotherapy a while ago. She is then followed towards death, with the films covering: prognostic information; treatment decisions, e.g. cessation of therapy; introduction of PC; and talking about death and dying. The videos are supplemented with exercises developed to reflect upon the contents of the films, learning objectives, presentations of specific communication skills, and references to relevant literature, intended for group or individual work at each intervention site.

The practical communication training is divided into two areas: (1) skills training; and (2) hands-on guidance. The first consists of local courses for small groups at the participating sites, focusing on specific communication challenges such as starting a discussion of prognosis and treatment intention, elucidating the patient’s preferences and provision of relevant information to patients facing termination of anticancer treatment and EoL. These are led by two experienced psychologists from the PALLiON education team and lasts for 1 full day. The hands-on guidance takes place after skills training. A local coach attends one consultation as an observing participant and gives the oncologist or PC physician feedback afterwards.

The structured educational program will be completed at all sites before patient inclusion and starts in the fall 2016. All lectures and instruction videos are available at the restricted access part of the PALLiON website and all participants in the intervention arm are encouraged to use this material for continuous discussions and updates. Access for participants in the control arm will be provided after study closure.

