**Methods:**

This is a national cluster-randomized trial (C-RCT) in 12 Norwegian hospitals. The trial investigates effects of early, systematic integration of oncology and specialized PC in patients with advanced cancer in six intervention hospitals compared with conventional care in six. Hospitals are stratified on the size of local catchment areas before randomization. In the intervention hospitals, a three-part complex intervention will be implemented. The backbone of the intervention is the development and implementation of patient-centered care pathways that contain early, compulsory referral to PC and regular and systematic registrations of symptoms. An educational program must be completed before patient inclusion. A total of 680 patients with advanced cancer and one caregiver per patient are included when patients come for start of last line of chemotherapy, defined according to national treatment guidelines. Data registration, clinical variables, and patient- and caregiver-reported outcomes take place every 2 months for 1 year or until death. The primary outcome is use of chemotherapy in the last 3 months of life by comparing the proportion of patients who receive this in the intervention and control groups. Primary outcome is use of chemotherapy in the last 3 months before death, i.e. number of patients. Secondary outcomes are initiation, discontinuation and number of cycles, last 3 months of life, administration of other medical interventions in the last month of life, symptom burden, quality of life (QoL), satisfaction with information and follow-up, and caregiver health, QoL, and satisfaction with care.

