##### Statistics

The design makes it possible to evaluate the effect of an early integration of oncology and PC at the institutional and patient levels across intervention and control arms, by comparing the use of chemotherapy in the last 3 months of life.

Analyses on the primary outcome will be performed when there are 300 patients in each arm with data on chemotherapy use in the last 3 months of life, which is the basis for the power estimation. Standard descriptive statistics will be used for background variables. Further, data will be analyzed by the intention-to-treat approach; mixed effect regression models will be used to analyze both primary and secondary endpoints in order to account for clustering. Logistic and linear regression models will be used respectively for binary and continuous outcomes and all models will be adjusted for potentially relevant baseline covariates at patient level, i.e. sex, age, diagnosis, performance status score, and baseline symptom scores. The analysis of the main outcome will also be adjusted by size of the catchment areas, which is the randomization stratification factor.

Survival analysis methods, i.e. Kaplan–Meier curves and Cox proportional hazards models with shared frailty terms to account for clustering and Kaplan–Meier curves, will be employed in order to model time to death. Sensitivity analyses to different methods will be applied to handle missing data in the secondary PROs: complete case analysis and multiple imputations. This also applies to patient- and caregiver-reported outcomes. Paper forms will be used to collect medical data and PROs for comparisons across arms.

Further, a potential effect of the intervention at each of the centers in the intervention arm may be evaluated at a later stage as an explorative outcome by comparing post-intervention data with historical data, e.g. on use of chemotherapy and number of readmissions/emergency admissions in the very last stages of life as appropriate.

The CONSORT recommendations for reporting RCTs will be followed. The CONSORT recommendations for reporting C-RCTs will be followed. IBM SPSS Statistics for Windows, version 25.0 (IBM Corp., Armonk, NY, USA) and STATA (Stata Corp. LCC, College Station, TX, USA) will be used.

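### Training before enrolment can change who enters the intervention arm, so comparability of the arms on the primary endpoint is not assured

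*Protocol article*

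**What the plan says.** All references are to the Protocol article.

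- **Order of events.** Hospitals are randomised within three size strata (Randomization, blinding, and study monitoring). The trial is described as non-blinded (Patient-centered care pathways). The concealment statement concerns the allocation of hospitals.
- **Training.** It takes place at the six intervention hospitals and covers prognostic tools, palliative chemotherapy, stopping treatment and talking about prognosis (The structured educational program). On timing: "Hence, the program is to be completed before patient inclusion in the PALLiON study, with a mandatory confirmation that it has been completed". Control staff get access only after the study closes.
- **Entry.** A patient must be judged in need of palliative care, with an anticipated life expectancy under 12 months, and be "Scheduled to start the anticipated last line of chemotherapy (definition: tumor directed systemic therapy") (Study population, Patients). The same item makes the time of inclusion depend on the decision about last line. The abstract describes entry as the "start of last line of chemotherapy, defined according to national treatment guidelines". Local principal investigators and study nurses include the patients (Organization).
- **Safeguards.** The control arm uses the same inclusion criteria (The control arm), and entry is limited to WHO performance status 0–2.
- **Adjustment.** "all models will be adjusted for potentially relevant baseline covariates at patient level, i.e. sex, age, diagnosis, performance status score, and baseline symptom scores" (Statistics). The main outcome is also adjusted for catchment-area size.

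**The concern.** Randomising hospitals balances hospitals. It does not protect the choice of patients when that choice is made later, by people who know the arm, on judgements that the intervention is meant to influence. There are several routes:

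- A trained clinician may decide with the patient against a last line. That patient is then never scheduled to start chemotherapy and never enters, although a similar patient may enter at a control hospital.
- Training in prognostication may instead lead staff to recognise short survival more often and to enrol more such patients.
- A line may be called the last at a different point in the disease.
- Patients already followed in a palliative care programme are excluded. Earlier referral at trained hospitals would make this filter depend on arm too.

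The primary endpoint is sensitive to all of these. Every enrolled patient is scheduled for chemotherapy, so one who dies soon after entry is likely to count as an event. A difference in prognosis at entry can therefore look like a difference in stopping behaviour, or hide one. Intention-to-treat analysis covers only patients who were enrolled, so it cannot recover those who never were.

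**Working it through.** **1. The plan's own figure.** Inputs from Sample size: "80% power at the two-sided 5% level to detect a 25% difference in chemotherapy use between the two arms"; "20% versus 45% in the treatment and control groups"; "predetermined number of 12 as the total number of clusters", so k = 6 per arm; and a total that "accounts for an ICC up to 0.08 even with a low" covariate correlation (r_adj) of 0.1.

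- Individually randomised n per arm, pooled variance: [1.960·√(2·0.325·0.675) + 0.842·√(0.20·0.80 + 0.45·0.55)]² / 0.25² = 53.9. With continuity correction it is 61.65.
- Adjusted: 61.65 × (1 − 0.1²) = 61.03.
- Patients per cluster: m = n(1 − ICC)/(k − n·ICC) = 61.03 × 0.92/(6 − 61.03 × 0.08) = 50.2, or about 301 per arm. The article states 300.
- Attrition: 300/0.88 = 340.9. The article states 340.

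The sample size reproduces and is not in dispute. Nor would a larger one help, because the issue is bias and not precision.

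**2. Spurious difference in favour of the intervention.** Assume no effect on stopping and a control rate of 45% (from Sample size). Assume also that a share f of control enrolees are short-survival patients who would not have entered at a trained hospital, and that a proportion q of them have the event. The intervention rate is then (0.45 − f·q)/(1 − f). Both f and q are assumptions; the article gives neither.

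| f | q | Intervention rate | Gap (points) |
|---|---|---|---|
| 5% | 70% | 0.415/0.95 = 43.7% | 1.3 |
| 10% | 80% | 0.370/0.90 = 41.1% | 3.9 |
| 20% | 80% | 0.290/0.80 = 36.25% | 8.75 |
| 20% | 90% | 0.270/0.80 = 33.75% | 11.3 |

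A second mechanism gives a similar size. Suppose a share s of intervention enrolments would not have entered under control practice and have an assumed risk of 20%. The gap is s × (45 − 20): 2.5 points at s = 10%, 5 at 20% and 10 at 40%.

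**3. Spurious difference against the intervention.** If trained staff enrol additional short-survival patients, so that they make up 10% of the intervention arm with an 80% event rate, the intervention rate is 0.90 × 45% + 0.10 × 80% = 48.5%. That is 3.5 points against the intervention.

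**4. Effect on the test.** With 300 per arm in clusters of 50, the design effect is 1 + 49·ICC. The effective n per arm is 300/3.94 = 76 at ICC 0.06 and 300/4.92 = 61 at ICC 0.08. The figures below use a normal approximation without continuity correction or covariate gain, which is why the starting power exceeds 80%.

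- No true effect, spurious gap of 5 points: the two-sided 5% test rejects in 9.6% (ICC 0.06) or 8.7% (ICC 0.08) of trials. With 10 points it rejects in 24.5% or 20.5%.
- True 25-point effect, selection the other way, ICC 0.08: power falls from 85% to 64% with a 5-point shift and to 40% with a 10-point shift.

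**5. What the planned adjustment leaves out.** The covariate list in Statistics is introduced as complete: sex, age, diagnosis, performance status and symptoms. The baseline e-CRF (Data registration by study personnel, Patients) also records date of diagnosis, stage, and site and number of metastases, and none of these is in the list. Albumin and C-reactive protein are recorded only if measured within the past 7 days. Number of previous lines is not a named field, and the entry for anticancer treatment carries a two-week limit.

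**The case against.** Training before enrolment is inherent to a hospital-level intervention, and no analysis can change that order. Both arms apply the same written criteria. The abstract ties last line to national guidelines. The eligibility item, which says that timing varies by diagnosis and is first line for some, fits a guideline rule by diagnosis, and *anticipated* is a natural word before treatment has started. The WHO 0–2 limit and the requirement of being able to consent keep out many of the frailest patients in both arms, and performance status and symptoms are in the model. The shares in the calculation are invented.

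Most of this stands as mitigation, and it narrows the routes described above. It does not close them. Identical criteria can be applied differently by staff with different training. A guideline line still leaves the survival judgement and the decision to schedule treatment. Performance status and symptoms capture only part of prognosis.

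A reader might infer that the intervention does change who enters, that the arms are not comparable, or that a lower intervention rate would be a product of selection. The article supports none of these. It contains no evidence that enrolment differs by arm, and the direction is open, as step 3 shows. Nor does it say that the treating oncologist alone decides entry; inclusion lies with principal investigators and study nurses.

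**Conclusion.** The design carries a risk of recruitment bias after allocation, and the safeguards reduce it without removing it. Comparability of the arms on the primary endpoint is therefore not assured. Direction and size are unknown. With a 45% control rate, no true effect, and assumed shares of 5–20% with event rates of 70–90%, the spurious difference in favour of the intervention is 1.3 to 11.3 points. With 10% extra short-survival patients at an 80% event rate it is 3.5 points the other way. Against the planned 25 points, the middle case of 3.9 points is about 16% (3.9/25). This is not enough to discredit a large observed effect, but it matters for a moderate one. The point warrants a change to the analysis and to how the result is qualified. It is not a ground for calling the comparison invalid.

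**What to change.** 1. Before analysis, add to the primary model the prognostic baseline variables that the e-CRF clearly collects: stage, site and number of metastases, and time since diagnosis. If the primary model is to stay as it is, make this a pre-specified sensitivity analysis. Use albumin and C-reactive protein only in a sensitivity analysis, because of the 7-day limit, and previous treatment line only if it can be derived from the recorded data.
2. Report numbers enrolled and baseline prognosis by arm and by hospital, and name recruitment bias as a limit on the conclusion.
3. Reconcile the abstract's guideline-based definition of last line with the anticipated last line in the eligibility criteria, so that readers know which was applied. This asks for clarification and proposes no clinical rule.

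The cost is small. Item 1 adds a few parameters and some missing values. At the planned rates there would be about 300 × 0.45 + 300 × 0.20 = 195 events to support them. Items 2 and 3 are reporting and wording. None of them alters eligibility, which would be unwise with recruitment open since March 2017 and due to end by 31 December 2020. The limit should be stated plainly: adjustment reduces bias that acts through the measured variables, but it cannot eliminate the bias or restore patients who were never enrolled.
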